**Methods/design:**

The aim of the study is to examine the effectiveness and efficiency of our new ICF (International Classification of Functioning, Disability and Health)-based rehabilitation for thermal injuries. Because of ethical reasons, we have chosen a prospective non-randomized design, which takes place at two different rehabilitation centers. At center A, a newly developed ICF-based rehabilitation program was established; at rehabilitation center B, a well-established rehabilitation program has existed for 20 years and is used as reference. The *primary research question* addresses the “Pre-post comparison of the physical and psychological outcome measurements,” *secondary question I* looks at the “Examination of the non-inferiority of the new treatment concept with the established concept,” and *secondary question II* is the “Analysis of the rehabilitation process based on the rehabilitation cycle.”

Only patients of the two burn rehabilitation centers who are insured by workers’ compensation will be asked to participate in this study to avoid outcome bias by insurance status. A physical examination (physical working capacity testing, grip strength, range of motion, and scar evaluation by Cutometer and Vancouver Scar Scale) and a standardized questionnaire battery (Burn Specific Health Scale-Brief , Short Form 36, Impact of Event Scale-Revised, the German version of the Symptom Checklist, the Freiburg Social Support Questionnaire, Patient/Client Satisfaction Questionnaire, Disabilities of the Arm, Shoulder and Hand, and Lower Extremity Functional Scale ) measure physical and psychological conditions. Data will be taken on admission, during stay, and on discharge of the rehabilitation program and at follow-up 3 and 12 months after discharge. A minimum of 162 participants will be enrolled in this clinical longitudinal, prospective, observational study.

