**Discussion:**

The proof of the effectiveness of the ICF-based rehabilitation program for thermal injuries will give evidence in a comprehensive way for the first time in this field. As result, a standardized rehabilitation concept will be introduced, which can be provided to other rehabilitation institutions treating thermal injuries.

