### Participants

The participants are admitted to the two burn rehabilitation centers in Germany dependent on proximity to their place of residence and availability of a contemporary treatment capacity. Preliminary analyses revealed an overall similarity between the both programs except for small differences: The rehabilitation program in center A contains more occupational therapy; at center B the program contains additional balneotherapy, which involves treatment of the skin by bathing in natural mineral water. Center A is located at the campus of a level 1 trauma center, whereas center B is located in a health resort. The duration of the rehabilitation is planned for 3 weeks in both facilities and can be extended individually.

Only patients of the two burn rehabilitation centers who are insured by workers’ compensation (*Deutsche Gesetzliche Unfallversicherung*) are asked to participate in this study to avoid outcome bias by insurance status. This approach is described in other studies for work-related burn injuries [11] or other orthopedic injuries [17]. This effect is described in terms of satisfaction, pain, functional measures, return to work rate, and adverse events [18].

To start a rehabilitation program, the acute treatment must be completed, and no surgical interventions should be planned during the rehabilitation period. Mostly stable skin and scar conditions are essential to initiate a multimodal treatment to support scar maturing. In case of residual defects, healing under conservative treatment should be expected within a short time. An additional requirement is a sufficient cardio-pulmonary exercise capacity. Table 2 presents the inclusion and exclusion criteria for the study.

**Table 2 Tab2:** Inclusion and exclusion criteria for the present study

Inclusion criteria	Written consent
	Sufficient knowledge of German in speech and writing
	Age ≥ 18 years Work-related accident
Exclusion criteria	Serious cognitive impairment (e.g., advanced dementia, acute psychosis, traumatic brain injury)
	Declining of the study

Data will be collected on prepared case report forms (CRFs) and by questionnaires and will be entered continuously into an Access database.

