#### Secondary research questions I and II

##### Secondary research question I

Are there any differences regarding the effect of the rehabilitation treatment on the outcome measures between the two centers (non-inferiority of center A to center B)?

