#### Statistical considerations

##### Sample size

We calculated the required case number for paired unilateral *t* tests for pre-post comparisons. Due to the small time intervals between the measurements, a small-to-medium effect size of 0.25 with an α-error probability of 0.05 is expected. An expected correlation of the measured values of at least 0.60 requires a power of 0.80. The power analysis revealed a sample size of 162 patients, *N* = 81 per center. Assuming a drop-out rate of 20%, as usually expected in a clinical trial, 92 patients per center would need to be enrolled.

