##### Statistical methods

Data will be collected continuously. For the statistical analysis, data will be checked for a normal distribution. Data are expressed by means with standard deviations and medians with interquartile range as appropriate. Categorical variables will be expressed as percentages.

Pre-post comparison (T1–T2) of the outcome measures will be tested by paired one-sided *t* tests. Longitudinal treatment effects will be tested by paired one-sided *t* tests between T1 and T3 and between T1 and T4.

The non-inferiority between the two centers will be proved with a power of 0.80 if differences are smaller than 0.4 standard deviation. Since randomized assignment to the centers is not possible, a potential selection bias between the samples will be matched by age, gender, TBSA, ABSI, and inhalation trauma. In case of an imbalance of the two samples, the analysis will be made along the procedure of propensity score matching.

A descriptive analysis of the patients’ rehabilitation goals and their linkage to the ICF categories will be performed. Patients’ and therapists’ assessments of goal achievement will be compared. The mean frequency of changing goals during the course of rehabilitation will be obtained. Furthermore, patients’ satisfaction with rehabilitation will be assessed with a qualitative interview, which will be evaluated by content, and the results of the CSQ-8 will be expressed by means and standard deviations.

The statistical evaluation will be carried out in cooperation with the statistician who participated in the design of the study (see Acknowledgements).

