The quasi-experimental prospective pre-post design was chosen due to ethical reasons, which do not allow a classical randomization. To balance this methodological limitation, we implemented the non-inferiority design between the two centers. The rehabilitation programs of the two centers were established independently from each other, at different points of time, but both are multidisciplinary ICF related and include the treatments recommended by national and international guidelines. Therefore, we do not hypothesize any difference in treatment effectiveness between the two centers.

A core element of our study is the assessment of patients’ rehabilitation goals, their possible change over the course of the rehabilitation treatment, and the patients’ satisfaction with goal achievement. The detailed observation of the rehabilitation process is one of the strengths of our study. We expect the ICF goals to change during the rehabilitation process from activities of daily living to more complex activities as well as work-related and social items. Assessment of patients’ rehabilitation goals and their satisfaction with goal achievement will also be an important factor for evaluation of our rehabilitation program. Rehabilitation studies in other domains show that a patient-centered, ICF-related program will have the most positive effect on the patients [31]. Furthermore, the rehabilitation goals of the patients will select the most relevant ICF categories and allow an adaption of the rehabilitation program. To our knowledge, no similar studies with an adult population exist until now in the literature.

We only include participants insured by worker’s compensation in order to avoid an outcome bias due to insurance status. This limits the possibility to generalize the results to patients of other rehabilitation centers or those with other types of insurance. However, we do not expect differences between our sample and patients of other burn rehabilitation centers in Germany.

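### The abstract poses the non-inferiority question for the treatment concept, but with one center per concept the comparison and its power of 0.80 support a conclusion about center A versus center B only

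*Protocol article*

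**What the plan says.** The protocol article names two different targets for secondary question I.

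- **Concept.** Abstract, Methods/design: "Examination of the non-inferiority of the new treatment concept with the established concept".
- **Center.** The section Secondary research question I sets the target at center level: "Are there any differences regarding the effect of the rehabilitation treatment on the outcome measures between the two centers (non-inferiority of center A to center" (the sentence closes by naming the second center). The Design section also describes a comparison of the two centers. Statistical methods gives the margin and power at that level: "The non-inferiority between the two centers will be proved with a power of 0.80 if differences are smaller than 0.4 standard deviation". The Discussion does the same: "To balance this methodological limitation, we implemented the non-inferiority design between the two centers".

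The new program runs at center A and the reference program at center B, with no second center for either. The Randomization section says that assignment depends on where the patient lives and on capacity. Under Participants the centers differ in more than program content: "Center A is located at the campus of a level 1 trauma center, whereas center B is located in a health resort". Against selection, Statistical methods offers matching on age, gender, TBSA, ABSI and inhalation trauma, with propensity score matching if the samples are imbalanced. No center effect is mentioned.

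**The concern.** A comparison of two centers and a comparison of two concepts are different inferences when each concept has a single center. Whatever is particular to center A (setting, staff, local practice) is carried by the new concept in the data, and likewise for center B and the established concept. The planned adjustment uses patient characteristics, so it can balance case mix but cannot touch a feature shared by every patient at a center. With one center per concept, the center effect cannot be estimated either.

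A positive result read in the abstract's terms would credit the concept with what may be due to the center. An inferior concept at a strong center could pass, and a sound concept at a weaker center could fail. This is the study's only comparative question, so the wording decides what the trial may conclude from it.

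**Working it through.** **Inputs from the article.** Margin 0.4 SD and power 0.80 (Statistical methods); 81 patients per center (Sample size). No alpha is given for non-inferiority. I carry over the one from the pre-post calculation: "We calculated the required case number for paired unilateral" *t* tests, with "a small-to-medium effect size of 0.25 with an α-error probability of 0.05 is expected".

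**Step 1: the plan's own figure.** Take patients as independent, SD = 1 and true difference 0.

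- SE = sqrt(2/81) = 0.157.
- Power = Phi(0.4/0.157 − 1.645) = Phi(0.90) = 0.816; with the *t* distribution 0.813.
- Patients needed per center: 2 × (1.645 + 0.842)² / 0.4² = 77.3, so 78.

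The stated 0.80 is reproduced. One-sided 0.025 does not fit: it needs 99 per center and gives power 0.72 at 81. The stated power therefore contains no center component, which is correct if the two centers are themselves the target.

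**Step 2: the same test read as a statement about the concept.** Let centers vary around their concept's mean with intraclass correlation ICC (total SD 1). With one center per concept:

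- True variance of the difference: V = 2·ICC + 2(1 − ICC)/81.
- Standard error the test uses: SE_w = sqrt(2(1 − ICC)/81).
- False non-inferiority rate at a true concept difference of −0.4 SD: 1 − Phi(1.645 × SE_w / sqrt(V)).
- Power at true difference 0 of a test that uses V as if known: Phi(0.4/sqrt(V) − 1.645).
- Limit of that power with unlimited patients: Phi(0.4/sqrt(2·ICC) − 1.645).

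The article gives no ICC. All values above 0 are assumptions.

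| Assumed ICC | sqrt(V) | SE_w | False non-inferiority | Power using V | Limit, unlimited patients |
|---|---|---|---|---|---|
| 0 | 0.157 | 0.157 | 5.0% | 0.82 | 1.00 |
| 0.01 | 0.211 | 0.156 | 11.1% | 0.60 | 0.88 |
| 0.02 | 0.253 | 0.156 | 15.6% | 0.47 | 0.64 |
| 0.05 | 0.351 | 0.153 | 23.7% | 0.31 | 0.35 |
| 0.10 | 0.471 | 0.149 | 30.1% | 0.21 | 0.23 |

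Worked line, ICC 0.05: V = 0.10 + 1.90/81 = 0.1235; 1.645 × 0.153/0.351 = 0.717; 1 − Phi(0.717) = 23.7%. A simulation of 200,000 trials also gave 23.7%.

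**Step 3: does enrolling more help?** At ICC 0.05 the rate is 22.9% with 74 per center (92 × 0.8 = 73.6), 23.7% with 81 and 24.8% with 92. The term 2·ICC does not depend on the number of patients, so the rate does not fall.

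**Step 4: sensitivity to alpha.** At one-sided 0.025 and 81 per center the rate goes from 2.5% to between 7.3% (ICC 0.01) and 26.8% (ICC 0.10).

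**The case against.** The strongest reply is that the operative text is already at center level. Secondary research question I, Design, Statistical methods and the Discussion all speak of the two centers, and for two fixed centers the center effect is part of the difference being estimated. The power of 0.80 and the 5% error then stand. This is right: a reader might infer that the non-inferiority test is mis-powered, and the documents do not support that.

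A reader might also infer that the error rate simply rises from 5% to about 24%. That figure depends on an ICC of 0.05, which the article neither gives nor calls typical; nor is it tied to any outcome or to change scores. With one center per concept the problem is confounding, and a single percentage would suggest precision that is not there.

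A third tempting reading is that transfer to other institutions hangs on the non-inferiority test, because the abstract says: "As result, a standardized rehabilitation concept will be introduced, which can be provided to other rehabilitation institutions treating thermal injuries". That sentence follows one about proof of effectiveness, which is the primary pre-post question. The Objective section likewise evaluates the new concept by pre-post comparison and process analysis, without naming non-inferiority. Some setting features, such as the mineral-water bathing at center B, may also be counted as part of the program.

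What the reply does not remove is the mismatch between the abstract and the methods over what a non-inferiority result would show. An analysis plan could not repair the concept reading, since no analysis separates concept from center here.

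**Conclusion.** The point holds as an inconsistency about the target of inference. The abstract's concept-level question cannot be answered by this design. The center-level question in the methods can be, subject to the usual limits of non-randomized allocation, and its stated power is correct.

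The direction of the problem for a concept-level claim holds for any ICC above 0. Its size is unknown: the 11% to 30% range illustrates assumed ICCs of 0.01 to 0.10 at one-sided 0.05, with 81 per center and a 0.4 SD margin, and should not be quoted as the trial's error rate.

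The sizing of the primary pre-post test is not affected. It reproduces on its own terms: standardized paired effect 0.25/sqrt(2 × (1 − 0.60)) = 0.280, giving 81 patients at one-sided 0.05 with power 0.80.

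**What to change.** 1. In the abstract, replace the concept wording of secondary question I with the wording of the methods: non-inferiority of center A to center B.
2. In Statistical methods, state that the power of 0.80 and the error rate apply to the comparison of center A with center B only, and state the one-sided alpha used.
3. Add a conclusion rule, for example: *A non-inferiority result is reported for the two centers, that is, program together with setting and staff. It is not used alone as evidence that the concept is non-inferior or transferable.*
4. Optional: beside the planned lower confidence limit, show limits widened by an added variance of 2 × ICC × SD² for ICCs of 0.01, 0.02 and 0.05, labelled as assumed, so that readers see how much center variation the result would tolerate.

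The cost is a few sentences and, if wanted, one small table. No patients, visits or measurements are added. The price is a narrower claim, which is the one that the design can support.

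### The 0.4 SD non-inferiority margin is larger than the 0.25 SD pre-post gain the study is planned on, so a non-inferiority verdict alone cannot show that centre A keeps centre B's short-term benefit

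*Protocol article*

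**What the plan says.** Secondary research question I asks: "Are there any differences regarding the effect of the rehabilitation treatment on the outcome measures between the two centers", and specifies this as "non-inferiority of center A to center B". The quantity compared is thus the effect of rehabilitation, with centre B as the reference.

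Statistical methods fixes the margin: "The non-inferiority between the two centers will be proved with a power of 0.80 if differences are smaller than 0.4 standard deviation". It gives no reason for 0.4, and does not say which SD, outcome or time point it refers to.

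The sample size has a different basis: "We calculated the required case number for paired unilateral *t* tests for pre-post comparisons". There, "a small-to-medium effect size of 0.25 with an α-error probability of 0.05 is expected", with short intervals between measurements given as the reason for the small value. It continues: "An expected correlation of the measured values of at least 0.60 requires a power of 0.80", and the result is: "The power analysis revealed a sample size of 162 patients, *N* = 81 per center". The 0.25 and the 0.4 are never related to each other.

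The Design section says the non-inferiority question was added because randomisation is not possible. The Discussion presents it as the counterweight to that limitation and adds that no difference between the centres is expected.

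**The concern.** A non-inferiority margin is the largest loss of effect one is willing to accept. If it exceeds the effect the reference programme is expected to deliver, passing the test is compatible with the new programme delivering nothing. Here the plan expects patients to gain 0.25 SD but tolerates a centre A shortfall of up to 0.4 SD. If centre B achieves the planned gain, the tolerated range for centre A's true change runs down to 0.25 − 0.40 = −0.15 SD.

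What is at stake is the meaning of a positive answer to secondary question I. An uncontrolled pre-post gain can include natural recovery, so the comparison with centre B is the only between-group evidence in the study. A reader told that centre A is non-inferior would take it to work about as well as the established programme. At this margin the verdict alone does not say so.

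**Working it through.** **Inputs.** Planned gain 0.25, α 0.05, one-sided paired t test, correlation 0.60, power 0.80, 81 per centre (Sample size); margin 0.4 SD with power 0.80 (Statistical methods); true difference between centres of zero when computing power (Discussion).

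**Step 1: which SD the 0.25 is in.** With a raw-score SD of 1 and correlation 0.60, the SD of the change is √(2(1 − 0.60)) = 0.894. The standardised change is 0.25/0.894 = 0.2795. A one-sided paired t test at 0.05 with power 0.80 (noncentral t) then needs n = 81, with power 0.802, which is the plan's figure. Treating 0.25 as already standardised by the change-score SD would need 101, and a two-sided test would need 103. Neither fits, so 0.25 is in raw-score SD.

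**Step 2: the plan's non-inferiority power.** Power = Φ(0.4/√(2/81) − 1.645) = Φ(0.4/0.157 − 1.645) = 0.816, and 78 per centre would give 0.80. At one-sided 0.025 the power is 0.721 and 99 per centre would be needed. The stated 0.80 therefore fits one-sided 0.05, which is used below.

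**Step 3: margin against planned gain.**
- Margin in raw-score SD: 0.40/0.25 = 1.60.
- Margin in change-score SD: 0.4 × 0.894 = 0.358 raw SD, and 0.358/0.25 = 1.43.

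The margin exceeds the gain on both readings.

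**Step 4: chance of a non-inferiority verdict.** Let B gain 0.25 SD and A change by x. With a confidence-bound test the probability is Φ((M − (0.25 − x))/SE − 1.645). SE is √(2/81) = 0.157 for raw scores and 0.894 × 0.157 = 0.141 for change scores.

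| Analysis | M (raw SD) | SE | A gains 0.25 | A gains 0 | A worsens by 0.10 | A worsens by 0.15 |
|---|---|---|---|---|---|---|
| Raw scores | 0.400 | 0.157 | 0.816 | 0.245 | 0.092 | 0.050 |
| Change scores, margin in raw SD | 0.400 | 0.141 | 0.885 | 0.282 | 0.099 | 0.050 |
| Change scores, margin in change SD | 0.358 | 0.141 | 0.816 | 0.190 | 0.056 | 0.026 |

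For example, row 1 with A gaining nothing: (0.40 − 0.25)/0.157 − 1.645 = −0.69, and Φ(−0.69) = 0.245. At one-sided 0.025 the zero-gain column becomes 0.157, 0.186 and 0.116.

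**Step 5: adding centre A's own test.** The setting is row 2, with A truly gaining nothing. A simulation that requires both non-inferiority and a significant one-sided pre-post gain in A passes in about 4% of trials, against 28% for non-inferiority alone. With A worsening by 0.10 SD the joint figure is about 0.3%.

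**Step 6: power at a margin equal to the planned gain.** Φ(0.25/0.157 − 1.645) = 0.48 on raw scores and Φ(0.25/0.141 − 1.645) = 0.55 on change scores. Power of 0.80 would need 198 or 159 per centre.

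**The case against.** The strongest reply is that the study already tests for the absence of benefit. Since 81 per centre is the full requirement for one paired test, each centre has about 0.80 power for its own pre-post change, and a centre A with no effect would usually fail that test. This stands in part: it is why the joint rule in Step 5 works. But the article does not say in words that the pre-post test is run by centre, and it does not make the non-inferiority verdict depend on it.

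Second, this is a secondary question. A reader might infer that the primary result falls with the margin. It does not: the primary pre-post test and its sample size do not use the margin. What is affected is the role given to the comparison in offsetting the missing randomisation.

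Third, a reader might infer that a worsening centre A would readily pass. The figures do not support that. A worsening of 0.10 SD passes in about 6–10% of trials, and a loss of 0.15 SD at no more than about the nominal 5%.

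Fourth, a reader might take 0.25 SD as the whole effect of rehabilitation. The article ties it to short measurement intervals, states no effect for 3 or 12 months, and gives no time point for the 0.4 SD. The ratio of 1.6 is shown only for the short-interval planning value.

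**Conclusion.** The concern holds in this form. The margin is 1.6 times the only planned effect (1.43 times on the change-score reading), so non-inferiority at 0.4 SD does not by itself show that centre A retains centre B's admission-to-discharge benefit. A centre A with no effect would be declared non-inferior in about 19–28% of trials. This should be fixed, but it does not invalidate the primary analysis.

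The result assumes a true gain of 0.25 SD in centre B, a correlation of 0.60, 81 analysed per centre, a single outcome, one-sided 0.05, and a verdict based on a confidence bound. The article does not state the last two for this comparison; Step 2 supports one-sided 0.05. If true gains are well above 0.25 SD, the margin is less extreme.

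A reader might also infer that 0.4 was chosen because it gives about 0.80 power at the sample size already fixed. The numbers are consistent with that, but the article does not say so, and the point does not depend on it.

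**What to change.** Change the wording for secondary question I as follows.

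- Report the matched, or propensity-score-matched, centre A minus centre B difference in change with its two-sided 90% CI (which corresponds to one-sided 0.05), and read it against the planned gain of 0.25 SD.
- Do not claim that centre A preserves centre B's effect on the 0.4 SD margin alone.
- If a non-inferiority statement is kept, allow it for an outcome only when centre A's own pre-post test on that outcome is also significant. State which SD and which time point the margin refers to.
- State that, at 81 per centre, power for a margin no larger than the planned gain (0.25 SD) is only about 0.48–0.55.

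The secondary objective need not be dropped, and the documents give no basis for any particular smaller margin.

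The change needs no new data and no change to the sample size. The cost is that a formal non-inferiority claim becomes less likely: with both centres truly gaining 0.25 SD, the joint rule cannot pass more often than the 0.80 power of centre A's own test, against 0.885 for non-inferiority alone in the change-score analysis with the margin in raw SD.

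### The matching set for the between-center comparison omits the T1 outcome value, and when matching applies is unsettled, which can leave confounding and reduce power

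*Protocol article*

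**What the plan says.** All places are in the protocol article.

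- **Adjustment set (Statistical methods).** Because patients are not randomized, "a potential selection bias between the samples will be matched by age, gender, TBSA, ABSI, and inhalation trauma". No other variable is named.
- **When it applies (same section).** The next sentence reads "In case of an imbalance of the two samples, the analysis will be made along the procedure of propensity score matching". No criterion for imbalance, matching ratio or caliper is given.
- **Target (Secondary research question I; Statistical methods).** The question is whether the effect of rehabilitation differs between centers. The margin is 0.4 SD with power 0.80. The text does not say whether T2 levels or changes from T1 are compared, which SD is meant, or what alpha is used.
- **What is collected (Table 3).** Every scored outcome except CSQ-8 is measured at T1.
- **Assumed correlation (Sample size).** "An expected correlation of the measured values of at least 0.60 requires a power of 0.80".
- **Time since burn (Initial patient characteristics).** It is not among the listed medical characteristics.
- **Setting (Participants; Randomization).** Assignment follows proximity and capacity. "Center A is located at the campus of a level 1 trauma center, whereas center B is located in a health resort".

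**The concern.** The comparison with center B is the study's only control, and the Discussion presents it as the counterweight to the lack of randomization. Confounding is therefore the main threat to it. The plan collects a variable it assumes to be strongly related to each later outcome, yet leaves that variable out of the set meant to remove selection bias. Balance on three burn-severity variables, age and gender need not balance grip strength, IES-R or BSHS-B at admission.

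The two sentences on matching also leave open whether the samples are always matched or only when imbalance is seen. If the second governs, an undefined trigger decides the method after the data are in. Matching can also leave patients unmatched, and the stated power contains no allowance for that.

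What is at stake is the non-inferiority conclusion of a secondary question. The primary pre-post question is not touched.

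**Working it through.** **Inputs from the protocol article.** 81 per center; r = 0.60; margin 0.4 SD; power 0.80; 92 enrolled per center with 20% drop-out. **Assumed here:** one-sided 0.05 for the non-inferiority test (the paired tests are one-sided at 0.05), true difference 0, and the sizes of T1 imbalance and of matching loss.

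**1. The plan's own figures.**
- Pre-post: 0.25/√(2(1 − 0.6)) = 0.2795. A one-sided paired t test at 0.05 then needs 81 patients (power 0.802). This agrees with 81 per center and confirms that r = 0.60 was used.
- Non-inferiority on the T2 scale: n = 2(1.645 + 0.842)²/0.4² = 77.3, so 78 per center. Power at 81 is 0.816 (0.813 by noncentral t). The stated 0.80 reproduces.
- On change scores with the margin still 0.4 of the T2 SD, the variance factor is 2(1 − 0.6) = 0.8. Then 62 per center suffice, and power at 81 is 0.885.
- At one-sided 0.025 the T2 scale needs 99 (power 0.721 at 81). The change scale needs 79 (power 0.812), so 0.80 also reproduces there.

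**2. Shift from a T1 imbalance d (SD units).** If patients with equal T1 values share the same expected T2 value, an unadjusted T2 difference shifts by 0.6d and a change-score difference by 0.6d − d = −0.4d. With SE = √(2/81) = 0.157 for T2 and 0.157 × √0.8 = 0.141 for change, the false non-inferiority rate at the margin is Φ(shift/SE − 1.645).

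| d (assumed) | T2 shift, A better at T1 | False NI | Change-score shift in A's favor, A worse at T1 | False NI |
|---|---|---|---|---|
| 0 | 0 | 5% | 0 | 5% |
| 0.1 | 0.06 | 10% | 0.04 | 9% |
| 0.2 | 0.12 | 19% | 0.08 | 14% |
| 0.3 | 0.18 | 31% | 0.12 | 21% |

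If center A is worse at T1, the T2 comparison is pushed against it instead, and power at 81 falls to 0.70, 0.55 and 0.40.

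**3. The trigger.** Suppose there is no systematic difference, 81 per center and five independent covariates. The chance that at least one absolute standardized difference exceeds 0.1 is 1 − (1 − 0.525)⁵ = 0.98; for 0.2 it is 1 − (1 − 0.203)⁵ = 0.68. The thresholds and the independence are assumed. The result is that the choice of threshold largely decides whether matching is used.

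**4. Patients left after matching (assumed numbers, one-sided 0.05).**

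| Per center | Power, T2 scale | Power, change scores |
|---|---|---|
| 81 | 0.816 | 0.885 |
| 73 | 0.780 | 0.855 |
| 65 | 0.737 | 0.817 |
| 57 | 0.688 | 0.771 |
| 49 | 0.631 | 0.715 |

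The row for 73 is 92 × 0.8 = 73.6, before any matching.

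**5. Adjusting for T1 in all patients.** Residual SD = √(1 − 0.6²) = 0.80, and 50 per center are needed. By noncentral t, power goes from 0.813 to 0.936 at 81 and from 0.776 to 0.913 at 73. At one-sided 0.025 the adjusted values are about 0.89 and 0.86. None of these allows for variance inflation from correlation between center and covariates, which is to be expected without randomization.

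**The case against.** **The T1 value may not be ignored.** Secondary question I asks about the effect of treatment, and the pre-post tests use differences from T1, so a between-center comparison of change is a natural reading. A reader might infer that the comparison disregards T1 altogether. The documents support this only for the matching set, and if change is compared the 0.18 SD figure does not apply. This stands.

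**Change scores are not necessarily biased.** The −0.4d shift assumes that the T1 difference regresses to a common mean. Allocation is by residence and capacity, not by T1. If a 0.3 SD difference reflects stable populations, change scores are unbiased and the T1-adjusted regression is off by 0.3 × (1 − 0.6) = 0.12 SD. This stands, and is why a change-score analysis should be kept beside the regression.

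**Matching only upon imbalance.** A reader might infer this from the second sentence alone, but the preceding sentence is unconditional. What remains is that the two do not settle the matter.

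**Lost power.** A reader might infer that matching will destroy the stated power. Without a ratio or caliper the loss cannot be computed, and on change scores at one-sided 0.05 a fall from 81 to 62 could be absorbed. Setting adjusted full-sample power against unadjusted matched power is also not like for like: against change scores at 81, the gain is from 0.885 to about 0.94.

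**Time since burn.** A difference between centers is only inferred from their settings. Entry requires completed acute treatment and mostly stable skin, and the case report form is not shown, so the accident date may already be recorded.

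**Condensed article.** Caliper, ratio and threshold may well sit in the full protocol. That does not answer the main point: the article does name the adjustment variables, and T1 is not among them.

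**Conclusion.** The point holds in limited form. The stated matching set omits the T1 outcome value and time since burn, and the text does not settle when matching applies. This can leave confounding in secondary question I and can reduce its power. The documents do not show that it will do either.

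On unadjusted T2 values the possible shift is 0.06 to 0.18 SD, that is 15% to 45% of the 0.4 SD margin, for assumed imbalances of 0.1 to 0.3 SD at r = 0.60. On change scores it is 0.04 to 0.12 SD in the opposite direction, and only under regression to a common mean. The reserve against matching losses is 3 patients per center on the T2 scale (81 against 78) and 19 on change scores (81 against 62), both at an assumed one-sided 0.05.

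Of the two omissions, the T1 value is the firmer; time since burn is secondary. The change should be made because it is nearly free and improves precision.

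**What to change.** Prespecify one main between-center analysis, applied whatever balance is observed: in all evaluable patients, a regression of the outcome at T2 (and likewise T3 and T4) on center, the T1 value of that outcome, age, gender, TBSA, ABSI and inhalation trauma. Add time from burn to admission if the accident date is recorded. For CSQ-8, which has no T1 value, use the same model without that term. State the alpha, and the SD to which the 0.4 margin refers.

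Keep two sensitivity analyses: propensity score matching with the T1 value in the score, and a comparison of change from T1. If they and the main analysis disagree on non-inferiority, report that.

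The cost is a few sentences of analysis text and slightly more analysis work, with no extra patients or visits; if the accident date is not yet recorded, it adds one date. The price in assumptions is reliance on the regression model, including that center is unrelated to prognosis given T1 and the covariates.
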